## Abstract

**Introduction:**

Worry and rumination are two forms of repetitive thinking characterised by their negative content and apparently uncontrollable nature. Although worry and rumination share common features and have been conceptualised as part of a transdiagnostic repetitive negative thinking (RNT) process, it remains unclear whether they share the same underlying cognitive mechanisms. This multisession experimental study investigates the tendency to make negative interpretations regarding ambiguous information as a cognitive mechanism underlying RNT. We compare multisession cognitive bias modification for interpretations (CBM-I) with an active control condition to examine whether repeatedly training positive interpretations reduces worry and rumination in individuals with generalised anxiety disorder or depression, respectively. Further, we examine the potential modulatory effects of engaging in RNT immediately prior to CBM-I.

**Design, methods and analysis:**

A community sample of individuals meeting diagnostic criteria for either generalised anxiety disorder (n=60) or current major depressive episode (n=60) will be randomly allocated to CBM-I with prior RNT, CBM-I without prior RNT (ie, standard CBM-I), or an active control (no resolution of ambiguity) condition. All conditions receive a 3-week internet-based intervention consisting of one initial session at the first study visit and nine home-based sessions of CBM-I training (or active control). We will assess and compare the effects of CBM-I with and without prior RNT on ‘near-transfer’ measures of interpretation bias closely related to the training as well as ‘far-transfer’ outcomes related to RNT and emotional distress. Impact on questionnaire measures will additionally be assessed at 1-month follow-up. Multigroup analyses will be conducted to assess the impact of CBM-I on near-transfer and far-transfer outcome measures.

Strengths and limitations of this studyOne of the first experimental studies to examine two forms of repetitive negative thinking (RNT), specifically worry and rumination, in people with a diagnosis of generalised anxiety disorder or depression, respectively, to investigate the extent to which these different forms of RNT are maintained by common or distinct processes.Assessing the causal role of a transdiagnostic cognitive process—interpretation bias—in maintaining different forms of RNT.Investigating moderators of multisession home-based cognitive bias modification for interpretations (CBM-I) effectiveness by comparing CBM-I with or without prior activation of RNT.Including an active control condition closely matched to training to examine whether modifying negative interpretations is critical for driving effects on interpretation bias, RNT and symptoms of anxiety and depression.The brief follow-up period (1 month) limits conclusions regarding long-term impact of training interpretations.

## Background and rationale

Worry and rumination are two forms of repetitive stereotyped thinking characterised by their negative content, overgeneral abstract style and—at pathological levels—by their apparently uncontrollable and perseverative nature. Both are associated with psychological distress, such as heightened anxiety and low mood,^1^
^2^ and are prevalent in a range of psychological disorders (see ref. 3). Moreover, worry and rumination are central to two particular emotional disorders. Uncontrollable worry about multiple topics is the key diagnostic criterion of generalised anxiety disorder (GAD),^4^ while rumination is a common feature of depression.^5^ Worry and rumination differ in thought content and in aspects such as temporal orientation (eg, future threats in GAD and past/ongoing concerns of failure in depression^6^). Their overlapping characteristics as well as their co-occurrence within individuals and across disorders have led worry and rumination to be conceptualised as a transdiagnostic process^3^
^7^ termed repetitive negative thinking (RNT). While worry and rumination may be characterised by a common thought process with distinct content, it remains unclear whether they are underpinned by the same cognitive mechanisms. This is especially important to elucidate given the role of RNT in maintaining clinical disorders (see ref. 8) and to inform approaches for therapeutic intervention. The present multisession experimental study aims to investigate interpretation bias—the tendency to make certain interpretations about ambiguous information—as part of a cognitive mechanism underlying RNT in relation to worry in GAD and rumination in depression.

Hirsch and Mathews^9^ identified three processes underlying RNT in the form of pathological worry: namely, emotional processing biases towards negative information, a verbal thinking style and deficits in attentional control. In the current study, we focus on emotional processing biases and specifically on negative interpretation bias, the tendency to habitually interpret ambiguous information as negative or threatening, to investigate whether negative interpretation bias plays a causal role in worry and rumination. Negative interpretations are prevalent in GAD and depression^10–13^ (for a review, see ref. 14). Its causal impact on worry and rumination has been examined using cognitive bias modification for interpretations (CBM-I), an experimental paradigm which repeatedly resolves ambiguous situations (often realistic scenarios capturing situations occurring in daily life) to favour certain (eg, positive) interpretations and thus aims to train a particular interpretive style (see refs. 14–16 for a review). In single experimental CBM-I sessions in clinical participants with GAD and non-clinical participants with high levels of trait worry, selectively training benign interpretations reduces worry,^17^
^18^ while consistently reinforcing negative interpretations increases state rumination.^19^ These findings point to a causal role of interpretation bias in worry and rumination. Thus, interpretation bias seems a promising candidate process to target using interventions designed to reduce worry and rumination and hence RNT.

Although pivotal for our theoretical understanding, single-session CBM-I studies are unable to address the sustained impact of changing interpretation bias. Multisession CBM-I, providing repeated training over several days to weeks and including a post-training follow-up period, is necessary to investigate the longer term training success of CBM-I on ‘near-transfer’ measures of interpretation bias and ‘far-transfer’ effects relating to central aspects of the disorder such as reductions in RNT, anxiety and depression symptoms. Initial multisession studies training positive interpretations revealed promising effects of CBM-I in reducing anxiety^20–22^ and depression.^23^
^24^ However, more recent multisession studies have presented mixed findings, with some showing that both CBM-I and active control conditions, in which no training effects are expected (eg, because positive and negative interpretations are presented with equal frequency) reduce negative interpretation bias.^25^
^26^ It is possible that repeated exposure even to 50% positive interpretations may lead to an incidental training effect over time and to reductions in anxiety and depression symptoms^26^
^27^ (see ref. 14, online supplementary materials, for considerations regarding the design of CBM-I studies). Thus, active control conditions which are closely matched to aspects of CBM-I (structure of sessions, number of sessions, experimenter contact, etc) but do not target resolution of ambiguity may be needed to demonstrate that effects of CBM-I are indeed driven by changes in interpretations. In the present study, we include an active control condition in which our training materials are adapted to remain ambiguous (no resolution of ambiguity); this was chosen over conditions in which materials are unambiguous (eg, ref. 27, study 2) which have also shown training effects.

Multisession CBM-I has the potential to shed light on the role of interpretation bias in sustaining worry and rumination and was developed to test hypotheses regarding causality. Previous studies on CBM-I have focused on its possible clinical utility (eg, it has been compared to cognitive behavioural therapy^22^
^26^) with a focus on reducing psychological distress (notably anxiety and depression), rather than with a view of better understanding cognitive mechanisms underlying RNT in clinical disorders. In this vein, although single-session studies have tailored training materials specifically to worry^18^ and rumination-related^19^ concerns, training materials in multisession studies often relate to broader symptoms of anxiety and depression rather than RNT. Thus, it is difficult to draw conclusions about the role of interpretations specifically in relation to RNT. In the present study, we tailor our CBM-I (and control) materials to common worry and rumination concerns with the hope of training interpretations made in the context of RNT (see also ref. 14 regarding the necessity to closely match materials used to assess or modify interpretation bias to ambiguity related to the key constructs—in this case RNT—being investigated).

The importance of considering the context in which interpretations are trained is further highlighted by research into another type of emotional processing bias, namely attentional bias towards negative or threatening information. Engaging in a period of experimentally induced worry in its typical verbal form increases attention to threat cues,^28^ indicating that worry may activate latent cognitive biases. Consistent with this (although in a different disorder), activating concerns in individuals with social anxiety disorder by exposure to idiosyncratic anxiety-provoking situations enhances the effects of subsequent attention training, leading to a greater reduction in social anxiety symptoms.^29^ This may be due to (re-)activation of emotional processing biases, rendering these more malleable and susceptible to modification, akin to findings in the memory reconsolidation literature.^30^

While providing tentative evidence that activating emotional processing biases via RNT (or exposure) may be beneficial in enhancing training effects, this has not yet been explored in relation to CBM-I. This is despite evidence that a depression-specific interpretation bias is most likely to be demonstrated in the context of depressive rumination.^31^
^32^ Building on this evidence, we seek to examine whether engaging in RNT prior to CBM-I, proposed to activate interpretation bias, will moderate the effects of CBM-I on interpretation bias, RNT and psychological distress. Although the attention bias literature points to a potential beneficial effect of prior RNT, it must be considered that Kuckertz *et al*^29^ focused on social anxiety rather than RNT. RNT, especially in its typical verbal form, depletes attentional control.^33–35^ Thus, it is possible that worrying or ruminating prior to CBM-I may hinder beneficial effects of training. Furthermore, effects of prior RNT may differ for the two diagnostic groups. As the first multisession study to test the proposed moderating role of RNT prior to training, we compare CBM-I with an induced period of RNT before training to CBM-I without such an induction (ie, standard CBM-I). Based on memory reconsolidation studies showing it is necessary to allow 10 min after reactivation for reconsolidation processes to be initiated (see ref. 30), participants in the condition with an induced period of RNT will engage in RNT on a recent RNT topic, followed by CBM-I relating to various worry or rumination topics (see also the Experimental conditions section). To further augment the impact of prior RNT on training, we then present CBM-I materials matched in content to participants' current RNT topic 10 min after their period of RNT. Participants in the standard CBM-I condition will be asked to indicate a recent RNT topic without subsequently engaging in RNT, and will also receive tailored CBM-I materials 10 min after completing a neutral (non-RNT) task.

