### Hypotheses

For both diagnostic groups, we predict that CBM-I with and without prior RNT will reduce negative interpretation bias, RNT (levels of worry and rumination) and psychological distress (levels of anxiety and depression) relative to the active control condition. Furthermore, we examine whether an induced period of RNT prior to CBM-I either enhances the effects of training (by activating underlying cognitive biases, as in attention bias research), or reduces training effects (potentially due to the additional demands placed on attentional control resources by RNT). Finally, and crucially given its proposed underlying role, we expect that effects of CBM-I on worry and rumination, anxiety and depression will be driven by changes in interpretation bias.

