## Methods

### Design

Individuals meeting Diagnostic and Statistical Manual of Mental Disorders Fifth Edition (DSM-V) diagnostic criteria for either GAD or current major depressive episode (MDD) will be randomly allocated to one of three conditions: CBM-I with prior RNT (henceforth CBM_RNT), standard CBM-I without prior RNT (henceforth CBM_STAND) or an active control condition (henceforth CONTROL). To investigate the impact of CBM-I on changing interpretation bias, near transfer will be assessed using measures of interpretation bias. To explore the impact of CBM-I on measures of RNT and psychological distress, far transfer will be assessed by changes to levels of worry and rumination (assessed using a behavioural task and self-report questionnaires) as well as self-report measures of anxiety and depression symptoms following 10 internet-based CBM-I or active control sessions over the course of 3 weeks. Impact on all questionnaire measures will additionally be assessed at 1-month follow-up.

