### Experimental conditions

All three experimental conditions comprise 10 sessions: 1 initial session at the first study visit and 9 sessions to be completed at home using a purpose-built online platform over the course of 3 weeks (participants are instructed to aim to complete 3 sessions per week). All online sessions begin with the prescenario RNT induction (CBM_RNT) or neutral task (CBM_STAND or CONTROL). Subsequently, participants listen to 50 audio clips (henceforth scenarios) per session and answer a corresponding question after listening to each scenario. All scenarios were audio-recorded by a professional actress and are presented to participants via headphones. In keeping with CBM-I research (see ref. 16), instructions in all conditions emphasise that participants should imagine themselves in the situations the scenarios describe and try to anticipate the ending of each scenario. Mood ratings are obtained after the RNT induction or neutral task and at the end of each session (see also below).

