This 3-min period of writing is intended to help participants activate themes of worry/rumination on the designated topic and is followed by a 2-min period of silent worry/rumination in participants' usual manner (akin to refs. 43 and 44):Now please continue to think as you usually would about [**one-line summary of topic**] for two minutes.You can close your eyes to do this, and a beep will sound at the end of the two minutes.If you notice your mind wandering to thoughts that are not distressing or worrying/ruminative, please try to bring your mind back to worrying/ruminating about [**one-line summary of topic**].Please press ‘next’ to begin.

Following this, participants complete ratings of their current level of worry, rumination, anxiety and depression, which serve as manipulation checks (see below).

*Neutral task**:* To minimise the opportunity for spontaneous RNT and to control for the time that participants are engaged in the RNT task, participants in the CBM_STAND and CONTROL conditions complete a neutral task. This 5-min task consists of reading a short story, divided into eight sections, and making a grammatical correctness judgement about the last sentence of each section. At the end of the eight sections, participants complete a comprehension question about the story content, designed to enhance engagement with the task. The presentation of each section is timed to ensure that the duration of the task is matched to the RNT induction. Participants read a different story at each session (order randomised across participants). Subsequently, participants complete the same ratings of current worry, rumination, anxiety and depression as participants in the CBM_RNT condition. A subset (five) of stories was initially piloted in N=23 participants (unrelated to the current study) and stories were judged to be emotionally neutral (mean valence rating on a 100-point visual analogue scale with anchors *very negative/very positive* =59, SD=1.41).

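### No arm combines the RNT induction with control scenarios, so CBM_RNT v CBM_STAND cannot separate moderation of CBM-I from the induction's own effect, and only CBM_STAND v CONTROL isolates interpretation training

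*Protocol article*

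**What the plan says.** The Design section has participants "randomly allocated to one of three conditions: CBM-I with prior RNT (henceforth CBM_RNT), standard CBM-I without prior RNT (henceforth CBM_STAND) or an active control condition". Under Prescenario task, "participants in the CBM_STAND and CONTROL conditions complete a neutral task", while CBM_RNT starts each session with a 5-minute induction (3 minutes of writing negative thoughts, then 2 minutes of silent worry or rumination). Experimental conditions and Procedure say the same. No arm pairs the induction with control scenarios.

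Two claims are built on these arms.

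- **Moderation.** Background and rationale asks whether prior RNT "will moderate the effects of CBM-I on interpretation bias, RNT and psychological distress" and gives the comparison that is to answer it: "we compare CBM-I with an induced period of RNT before training to CBM-I without such an induction (ie, standard CBM-I". Study objectives, Hypotheses and the Discussion repeat the idea as RNT modulating, enhancing or reducing what training does. The Abstract's strengths list includes the study of moderators.
- **Causal role of interpretation bias.** The strengths list gives as one item: "Including an active control condition closely matched to training to examine whether modifying negative interpretations is critical for driving effects". The Hypotheses section then reads "we predict that CBM-I with and without prior RNT will reduce negative interpretation bias", along with RNT and distress, relative to CONTROL. It expects the effects on RNT and symptoms to be driven by change in interpretation bias.

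The only limitation in that list is the short follow-up.

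**The concern.** Moderation is a statement about an interaction: is the effect of training (v control) different when RNT comes first? Answering it needs the training effect with the induction and the training effect without it. The trial has the second but not the first, because nobody receives the induction followed by control scenarios.

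Repeatedly writing and thinking about one's own concerns could change RNT by itself, down through habituation or up through rehearsal. The article gives its own reasons to take such an effect seriously. Background and rationale says that induced worry raises attention to threat, that RNT drains attentional control, and that a depression-specific interpretation bias shows most readily in the context of rumination. Some bias measures also follow the induction within the same session: the recognition memory test repeated after the first online session, and the test trials embedded in every session.

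At stake is what may be concluded. A difference between CBM_RNT and CBM_STAND could be described as RNT strengthening or weakening CBM-I when no interaction exists. A difference between CBM_RNT and CONTROL could be credited to interpretation training when part of it comes from the induction.

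**Working it through.** The plan gives no figure on this point. The inputs are the arm definitions (Experimental conditions; Prescenario task), the target of 20 per condition in each diagnostic group (Sample size), and the definition of completers as at least 8 of 10 sessions (Statistical methods).

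**1. What each contrast estimates.** Let μ be the mean under control scenarios with the neutral task, T the training effect after the neutral task, R the induction's own effect under control scenarios, and TR the interaction, which is the moderation.

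| Arm | Mean |
|---|---|
| CONTROL | μ |
| CBM_STAND | μ + T |
| CBM_RNT | μ + T + R + TR |
| Control scenarios + RNT (does not exist) | μ + R |

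- CBM_STAND − CONTROL = T
- CBM_RNT − CBM_STAND = R + TR
- CBM_RNT − CONTROL = T + R + TR

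The third contrast is the sum of the first two, so there are two independent contrasts for three unknowns. The design matrix has rank 3 for 4 parameters. T is estimable. R, TR and the training effect after RNT (T + TR) are not. With the fourth cell the rank would be 4 and all would be estimable.

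**2. Illustration (values assumed; benefit coded positive).** Take T = 0.5 SD and TR = 0. With R = +0.3, CBM_RNT v CONTROL is 0.5 + 0.3 = 0.8 SD; with R = −0.3 it is 0.5 − 0.3 = 0.2 SD. CBM_RNT v CBM_STAND is +0.3 or −0.3 SD although there is no moderation.

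**3. How often that would be significant.** Two-sided t test at 0.05 (the article does not state sidedness), df = 2n − 2, noncentrality R√(n/2), TR = 0:

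| R (SD, assumed) | 20 per arm | 40 per arm (both diagnostic groups pooled) |
|---|---|---|
| 0 | 5% | 5% |
| 0.2 | 9.5% | 14% |
| 0.3 | 15% | 26% |
| 0.5 | 34% | 60% |
| 0.8 | 69% | 94% |

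These are correct rejections of R + TR = 0. They become false positives only if read as tests of TR.

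**4. Does another element of the plan supply R?** No. The manipulation check compares state ratings after the induction with those after the neutral task. That shows whether the induction worked at the time, not what it does to the outcomes without training.

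**5. Exposure before the visit-2 breathing focus task.** That task contains its own 5-minute worry or rumination period. Counting visit 1, the sessions and visit 2, a CBM_RNT completer has had 1 + 8 + 1 = 10 to 1 + 10 + 1 = 12 instructed RNT periods; the other arms have had 1 + 1 = 2.

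**The case against.** - **The comparison is openly defined.** The article says that it compares CBM-I with and without an induction, and the Discussion speaks of two versions of CBM-I and of optimising training. For the practical question of which version works better, CBM_RNT v CBM_STAND is the right randomised contrast. This stands; only the moderation wording goes further than the contrast allows.
- **The central causal question is still tested.** A reader might infer that the trial cannot isolate interpretation training at all. The documents do not support that. CBM_STAND and CONTROL share the neutral task, and condition enters the models with three levels, so a contrast unconfounded by the induction is available.
- **R is not shown to be non-zero at outcome.** The background describes RNT's effects on attention, not effects that last into later outcomes, and the final home session falls no later than the day before visit 2. This stands: an own effect is plausible, not demonstrated. But a moderation claim needs R = 0, and that is neither stated nor shown.
- **Near-transfer and mediation analyses offer some protection.** A habituation effect that left interpretation bias unchanged should show in neither. So it would be too strong to say that an induction effect *would* be reported as evidence for interpretation bias. These analyses still do not identify TR, and mediation that uses CBM_RNT v CONTROL, or pools the CBM-I arms, carries R with it.
- **The rehearsal point is small.** The breathing focus outcome is intrusions during breathing periods, one of which precedes the provocation, and the induction is mostly writing. It merits a line among the limitations and no more.

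**Conclusion.** The concern holds in this form: the three-arm design cannot separate moderation of CBM-I by prior RNT from the induction's own effect unless that own effect is assumed to be zero, and CBM_RNT v CONTROL does not isolate interpretation training. The non-identifiability follows from the arm definitions alone. The error rates of 15% to 69% at 20 per arm rest on assumed own effects of 0.3 to 0.8 SD with no interaction, and carry no more weight than those assumptions.

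It would go too far to say that moderation can in no circumstances be tested, since R = 0 would make the contrast a valid test. CBM_STAND v CONTROL remains sound, as does the net effect of adding the induction. No allocation, outcome or data collection has to change. The point should be fixed because it changes what the trial may conclude, but it is not a fatal flaw.

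**What to change.** Add no arm and collect no new data.

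1. Name CBM_STAND v CONTROL as the contrast for the causal role of interpretation bias. Base that conclusion and its mediation analysis on it, without pooling the two CBM-I arms for this purpose.
2. Report CBM_RNT v CBM_STAND as the total effect of adding an RNT induction to CBM-I. In the Abstract's strengths list, Background and rationale, Study objectives, Hypotheses and Discussion, either replace the wording about moderating, modulating or enhancing CBM-I, or state the assumption that the induction has no effect of its own.
3. Report CBM_RNT v CONTROL as the effect of the combined package.
4. List the missing control-plus-RNT cell as a limitation. Note briefly that CBM_RNT completers reach the visit-2 breathing focus task after more instructed RNT (10 to 12 periods v 2, counting the one in that task).

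**Cost.** The moderation claim becomes more modest. Where the CBM-I arms would otherwise have been pooled, the causal contrast uses 20 v 20 per diagnostic group instead of 40 v 20. The standard error is then √(1/20 + 1/20) = 0.316 SD instead of √(1/40 + 1/20) = 0.274 SD, about 15% larger.

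**Why not a fourth arm.** At submission 59 participants had completed. A further 20 per diagnostic group would raise the total from 120 to 160 and make the interaction estimable, but power within a diagnostic group would be only 20% for an interaction of 0.5 SD and 42% for 0.8 SD (assumed sizes, two-sided 0.05). Reaching 80% would take 127 or 50 per cell.
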